### Sample Size

We have been conservative in estimating our ability to enroll and retain participants, by assuming that 50% will refuse to participate and 50% of enrolled adolescents will drop out. A total of 160 adolescents are being invited to participate with the expectation that we will enroll 80 adolescents (40 assigned to each study arm) and retain 40 adolescents (20 per arm) by module 8 completion (post-intervention). In keeping with the standard goals of a pilot RCT, a sample size of 40 adolescents at post-intervention (20 per arm) will provide sufficient data on the primary outcome to calculate a sample size based on 90% power for a full-scale RCT [48,49].

### Treatment Condition

#### Essential Clinical Components

Consistent with published CBT treatment recommendations [20,21,22], the *Breathe* program consists of 8 core CBT treatment modules (8 weeks of treatment; Figure 2) that involve (1) multi-media based education about anxiety problems and approaches to overcoming anxiety (eg, reviewing why exposure exercises are important), (2) self-assessment activities to determine level of treatment and safety needs (Figure 3), (3) activities to teach adolescents about anxiety sensitivity, how to identify anxious thoughts, and how to develop realistic thinking about anxiety-producing situations (Figure 4), (4) coping and relaxation skill activities with self-assessment of performance and rewards, (5) development of a hierarchy of feared situations and steps for gradual and repeated exposure to feared situations (using imagery and *in vivo* activities), (6) contingency management (examining the function of anxiety from a reinforcement perspective) and modeling (viewing videos of others confronting feared situations), and (7) skills for maintenance and relapse prevention. Animations, embedded video, audio playback, graphic novel style vignettes, image maps, timed prompts and on screen pop-ups provide an interactive and multimodal experience to promote sustained engagement with the treatment content across modules.

Adolescents are instructed at the beginning of the trial to use the program weekly. Adolescents who do not log in for one week receive an e-mail encouraging them to log in to complete their weekly module. During the program, adolescents have access to an *Ask the Expert* feature where they can e-mail a trained research team member with questions regarding the program and/or treatment. *Breathe* successfully underwent iterative usability testing cycles with five clinicians and five adolescents prior to the pilot study to ensure adherence to CBT therapeutic principles, developmental appropriateness for the target age group, satisfaction, and engagement with the multi-media content.

**Figure 2 figure2:**
[figure not shown]
A screenshot of the Breathe program home screen.

**Figure 3 figure3:**
[figure not shown]
A screenshot of a weekly self-assessment activity.

**Figure 4 figure4:**
[figure not shown]
A screenshot of a learning activity.

#### Persuasive Design Mechanisms

*Breathe* is delivered via the Internet-based platform IRIS, which supports the integration of persuasive design mechanisms [50] for Internet-based interventions that are proven to encourage user engagement. Through the adaptive informatics architecture of IRIS, *Breathe* personalizes the program for adolescents via three primary mechanisms: *tailoring* content (ie, providing custom information and feedback to the adolescent based on their actions); *self-monitoring *(ie, enabling the adolescent to track their own behavior toward intended outcomes); and automated *suggestions/reminders* (ie, providing adolescents with information at the right time and the right context to help them keep on track). For example, an adolescent who indicates issues with alcohol or other drug use would receive material on these topics, while an adolescent who indicates alcohol or other drug use is not an issue would not. *Breathe* also engages the adolescent’s parent(s) by sending e-mails with educational materials about the nature of adolescent anxiety and highlights of key topics their child is working on in the program. Adolescents are given the choice as to whether they want parents to receive these e-mail updates.

#### Safety Monitoring

The risks for adolescents participating in this pilot trial are considered minimal, but those in the treatment group are monitored each time they start and finish a module in the intervention program, to assess clinical functioning. Adolescents complete a *check-in* and *check-out* whereby they answer questions related to anxiety symptoms and indicate whether they are having thoughts of self-harm or harming others. This *check-in/check-out* is a typical clinical feature of CBT programs. The research team monitors the adolescents’ answers through automated indicators built into the IRIS program. If IRIS flags a safety issue (eg, decompensation in anxiety symptoms, thoughts of self-harm), a research team member contacts the adolescent and their parent(s) by phone follow-up within 36 hours and directs them to emergency services if the adolescent requires more immediate care. Additionally, the adolescent is automatically directed onscreen to a safety video on self-harm and a pop-up box appears in the program encouraging the adolescent to notify a parent/guardian of their thoughts and to seek immediate help. Access to the *Ask the Expert* feature in *Breathe* and e-mail contact also allow adolescents to identify distressing issues that may be activated during treatment. Such adolescents are re-assessed to determine if continuing in the study is advisable. Those adolescents not able to use the program independently or who are struggling with additional mental health issues may be referred to a higher level of care. Any serious adverse event will be reported to the institutional ethics board according to the standard operating procedures. Adolescents randomized to the control group are provided with contact information for local emergency resources (crisis lines, emergency department and/or other crisis mental health resources).

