We are also screening for risk of suicide using the Ask Suicide-Screening Questions (ASQ) [39]. The ASQ is a brief 4-item instrument originally validated for use in emergency departments with high sensitivity for identifying the risk of suicide [39]. A “yes” response to questions 1 (“In the past few weeks, have you wished you were dead?”), 2 (“In the past few weeks, have you felt that you or your family would be better off if you were dead?”) or 4 (“Have you ever tried to kill yourself?”) on the ASQ involves a safety-follow up phone call from a research team member to evaluate intent/severity/immediacy of risk before deciding on adolescent eligibility. Adolescents who respond “yes” to question 3 on the ASQ (“In the past week, have you been having thoughts about killing yourself?”) are excluded from the study and receive brief telephone based support from a research team member to evaluate intent/severity/immediacy of risk and encourage the adolescent to seek further mental health care/crisis care.

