### Control (Minimal Intervention) Condition

Adolescents assigned to the control group are provided with access to a static webpage that houses suggested anxiety-related trade publications, print-based workbooks for adolescents, and the names of organizations and websites where the adolescent might find support. There is no interactivity or personalization included in the webpage. Adolescents assigned to the control group are provided with the option to use the *Breathe* program at the end of their 8-week control group participation. At that time, the study will follow the same processes to monitor safety and support adolescents who may require additional help, as detailed above.

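### After screening, thoughts of self-harm are actively asked only in the Breathe arm and only at module use, so harms are ascertained unequally by arm and by engagement

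*Protocol article*

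**What the plan says.** All references are to the protocol article.

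- **Breathe arm.** Under Safety Monitoring, "those in the treatment group are monitored each time they start and finish a module in the intervention program, to assess clinical functioning". At these check-ins and check-outs "they answer questions related to anxiety symptoms and indicate whether they are having thoughts of self-harm or harming others". Adolescents can also raise problems themselves: the Ask the Expert feature and "e-mail contact also allow adolescents to identify distressing issues that may be activated during treatment".
- **Breathe adolescents who stop using the program.** Under Essential Clinical Components: "Adolescents who do not log in for one week receive an e-mail encouraging them to log in to complete their weekly module". No safety question is described for this situation.
- **Control arm.** Under Safety Monitoring: "Adolescents randomized to the control group are provided with contact information for local emergency resources". Under Control (Minimal Intervention) Condition, the webpage is static, and Breathe is optional once the 8 weeks are over. Only then does the same monitoring apply: "At that time, the study will follow the same processes to monitor safety and support adolescents who may require additional help".
- **Who can be enrolled.** Under Participants, a yes to ASQ question 1, 2 or 4 (recent wish to be dead, feeling that self or family would be better off, past attempt) "involves a safety-follow up phone call from a research team member to evaluate intent/severity/immediacy of risk before deciding on adolescent eligibility". A yes to question 3 excludes. Table 1 shows the ASQ at screening only.
- **Expected loss.** Sample Size assumes that "50% of enrolled adolescents will drop out".
- **Other sources of information.** Controls complete the MASC2 at baseline and 8 weeks. Use of co-interventions, including emergency visits, is self-reported at the post-intervention assessment with no restriction by arm. Serious adverse events go to the ethics board.

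**The concern.** Adolescents with some positive suicide-risk items can enter the trial and be randomized to either arm. From then on, the only described question about self-harm thoughts sits inside one of the two interventions and appears only when that intervention is used. Whether a case is found then depends on allocation and, within the Breathe arm, on continued use.

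Two things are at stake. First, a tally of flags by arm would show events for Breathe and none for controls even if the true rates were equal. It could be misread as harm from Breathe or as reassurance about the webpage. Second, the Discussion plans a full-scale trial against the same kind of static-webpage control, so the unequal ascertainment could carry over into a trial where harms will be compared.

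**Working it through.** **1. The plan's own numbers (Sample Size).** Invited 160, refusal 50%: 160 × 0.5 = 80 enrolled, 40 per arm. Dropout 50%: 80 × 0.5 = 40 retained, 20 per arm. The stated chain reproduces.

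**2. Planned self-harm questions between randomization and week 8.**

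| | Breathe (40) | Control (40) |
|---|---|---|
| Self-harm question | at each module start and finish | none described |
| ASQ | not scheduled | not scheduled |
| If inactive | e-mail prompt to log in | not applicable |
| MASC2 | 8 weeks / end of module 8 | 8 weeks |
| Self-reported care, including emergency visits | post-intervention | post-intervention |
| Reporting of serious adverse events | yes | yes |

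The last three rows are common to both arms. The first two of them come once, at the end, and need a response. The third reports an event that has become known; the article describes no question that would find it. None is described as asking about thoughts of self-harm.

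**3. Numbers affected.**
- Controls without a planned self-harm question in the 8 weeks: 40 of 40.
- Breathe adolescents who may lose the question for part of the 8 weeks: 40 × d, where d is dropout. At the plan's d = 50%, this is 40 × 0.5 = 20. For assumed d of 0%, 25% and 75%, it is 0, 10 and 30.

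The 20 is an upper figure for the plan's assumption. Sample Size counts loss by completion of module 8, and those who stop will have been asked at each module they opened before stopping.

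**4. What equal true rates would look like.** The documents give no rate of self-harm thoughts, so p = 5%, 10% and 20% per arm are assumptions. Expected true cases per arm are 40 × p. Expected check-in flags in Breathe are 40 × p if nobody stops, and 40 × p × 0.5 if half stop before their event.

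| Assumed p | True cases, each arm | Flags, Breathe (no dropout) | Flags, Breathe (half stop first) | Flags, control |
|---|---|---|---|---|
| 5% | 2 | 2 | 1 | 0 |
| 10% | 4 | 4 | 2 | 0 |
| 20% | 8 | 8 | 4 | 0 |

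Identical true rates appear as an excess in Breathe, and the Breathe count itself falls as engagement falls.

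**5. What an 8-week question in both arms could recover.** With 50% responding, and response unrelated to self-harm thoughts (an assumption), about 20 per arm answer. The most that could be captured is 40 × 0.5 × p = 1, 2 or 4 per arm for the three rates, the same in both arms. Thoughts outside the recall period of the question would still be missed. ASQ questions 1 to 3 look back a week to a few weeks, and question 4 is lifetime.

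**The case against.** - **Comparative safety is not an aim.** None of the six pilot objectives concerns it, and Statistical Analyses plans no comparison of flags by arm. The check-in is presented as an ordinary part of a CBT program. This stands: the plan does not commit the misreading, and the point is an improvement to measurement, not an error against the stated aims. Detection of self-harm thoughts in enrolled adolescents with positive screening items still matters without a formal comparison.
- **The detail may be in documents not shown.** Serious adverse events follow standard operating procedures, and Table 1 is an outcome schedule that omits the check-ins too. This stands for how serious events are handled. It does not answer the main point, because the article states positively who is monitored, when, and what controls receive instead.
- **Stronger readings a reader might infer.**
  - *That worsening is assessed only in Breathe.* It is not: controls complete the MASC2 at 8 weeks.
  - *That harms in controls or inactive Breathe adolescents go wholly unseen.* They do not: emergency visits and other care are self-reported in both arms, serious adverse events are reportable, and Breathe adolescents can contact the team.
  - *That 60 of 80 (75%) are unmonitored.* The sum 40 + 20 adds controls who are never asked to Breathe adolescents who are asked for part of the time.
  - *That the sections on screening, monitoring and the control condition contradict one another.* They cover different stages and are consistent.
- **One 8-week questionnaire would itself miss many.** This stands, as step 5 of the working shows.

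**Conclusion.** The point holds in a limited form. After screening, the article describes active questions on self-harm thoughts only in the Breathe arm and only at module use. Ascertainment therefore differs by arm and by engagement, and check-in flags cannot support a comparison of harms. All 40 controls have no planned self-harm question in the 8 weeks. Up to about 20 of 40 Breathe adolescents may lose it for part of that time, on the plan's own 50% dropout. The case counts in the working rest on assumed rates and are illustrations only.

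The documents do not support saying that harms go undetected altogether, or that the pilot fails an objective it set itself. This is a low-cost improvement worth making, especially as the pilot is meant to shape the full-scale trial.

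**What to change.** 1. Add the existing check-in question on self-harm thoughts, or the ASQ already in use, to the 8-week online assessment for every randomized adolescent. Send it by calendar date whether or not modules were completed; the Breathe post-treatment assessment is currently described as at 8 weeks or the end of module 8.
2. Report the answers by arm with the number who responded, separately from flags raised at module check-ins.
3. State that check-in flags are not to be read as a between-arm comparison of harms.

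**Cost.** A few existing questions go into an online assessment already scheduled in both arms. The downside is some additional positive answers for the research team to handle. How they are handled in each arm is for the investigators to state. The change reduces the inequality without removing it: non-responders, and thoughts outside the recall period, would still be missed, and Breathe adolescents would still be asked more often.

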### Control (Minimal Intervention) Condition

Adolescents assigned to the control group are provided with access to a static webpage that houses suggested anxiety-related trade publications, print-based workbooks for adolescents, and the names of organizations and websites where the adolescent might find support. There is no interactivity or personalization included in the webpage. Adolescents assigned to the control group are provided with the option to use the *Breathe* program at the end of their 8-week control group participation. At that time, the study will follow the same processes to monitor safety and support adolescents who may require additional help, as detailed above.

### Statistical Analyses

Adolescent reports of anxiety, intervention acceptability and adherence, use of co-interventions, recruitment and retention rates, and demography will be described by numerical summaries (mean, frequency, range, and standard deviation [SD]). The mean difference in primary outcome change scores (and SDs) from baseline to the completion of module 8 (post-intervention) will be calculated with 95% CIs. SD values from the primary outcome change scores will be used to guide the full-scale RCT sample size calculations [51]. Adolescent global ratings of change (within the ranges of +2 to +3 or -2 to -3 for reported change using the 10-point Likert scale) will serve as the estimate for the MCID value [52]. The study recruitment rate (number of adolescents enrolled during the study recruitment period) and the retention rate (number of adolescents retained at the 3-month follow-up as indicated by MASC2 completion) will be calculated. These rates will be used to determine the number of study sites and time period needed for a full-scale RCT. Frequencies and proportions (with 95% CIs) will be used to describe categorical variables (eg, gender). We will summarize characteristics of completers (>75% of modules) and non-completers, and conduct tests of association to identify particular adolescents (eg, by gender) that may benefit from additional measures to maintain engagement, and will explore potential confounders (eg, age, sex, co-morbidity) that may be adjusted for in the full-scale RCT. Mean costs (and SDs) will be calculated (with 95% CIs) using published recommendations [46,47]. To account for the amortization of intervention use after upfront costs, we will distribute the investment costs over a 3- to 5-year investment time duration using a 5% societal interest rate and using 3% and 0% rates in the sensitivity analysis. Costs for reported co-interventions (health care services) will be estimated using Alberta costing and using 2015-dollar values.

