Three recent systematic reviews of the literature have shown that self-led, computer-based and computer-assisted CBT, in combination with in-person or therapist-guided care, are viable and effective treatment approaches for children and adolescents [30,31,32]. Studies of treating adolescents using Internet-based CBT are limited to two [33,34], but provide important evidence and methodological considerations for other treatment studies. In a study targeting social fears (mainly centered on public speaking) in high school students who met the diagnostic criteria for social anxiety disorders, Tillfors et al. found that significant reductions in anxiety symptoms and improvements to mood were achieved post-intervention and maintained at one-year follow-up [34]. These treatment effects were noted as comparable to those achieved through traditional face-to-face CBT. Focusing on the treatment of adolescents who had a “markedly disturbing/disabling” anxiety disorder (predominantly generalized anxiety disorder and social phobia), Spence et al. also found that Internet-based CBT with minimal therapist support was equally efficacious as face-to-face CBT delivery in reducing anxiety symptoms post-intervention and up to one-year post-treatment [33]. The parents of participating adolescents also took part in this online program. In both studies, methods to improve treatment compliance, and the impact of compliance on treatment outcome, were noted as issues that required further investigation. Tillfors et al. reported that, of nine online modules available to complete within a 9-week period, the average number of completed modules was 2.9 [34]. Spence et al. noted that on average, adolescents and parents completed 7.5/10 and 4.48/5 sessions, respectively [33].

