### Measures

#### Primary Outcome Measure

Change in anxiety symptoms in adolescents will be measured using the total score from the Multidimensional Anxiety Scale for Children (MASC2; 50 items). The MASC2 is one of the most widely used self-report measures in clinical trials in adolescents with anxiety disorders. It assesses physical symptoms, social anxiety, harm avoidance, separation/panic, and total anxiety, and has excellent 3-month test-retest reliability [40] and excellent validity [41,42]. Adolescent self-report is desirable because of the internalizing nature of anxiety [43]. The MASC2 is administered online via Intelligent Research Intervention Software (IRIS) to adolescents in the treatment group at three data collection time points: baseline (pre-treatment), 8 weeks/end of 8^th^
*Breathe* module (post-treatment) and 3 months post-treatment (follow-up). Adolescents in the control group complete the MASC2 at baseline and 8 weeks after study enrolment via IRIS. Table 1 outlines screening and outcome measurement time points.

**Table 1 table1:** Outcome measurement schedule.

	Study time points					
	Study eligibility screening	Baseline	8 weeks (postintervention)	20 weeks (3-month follow-up)	End of study enrolment period (22 months from trial start)	End of data collection period (27 months from trial start)
Demography	X					
SCARED	X					
ASQ	X					
Co-intervention use/costs			X			
MASC2		X	X	X		
MCID			X			
Treatment satisfaction			X			
Treatment adherence			X			
Number of adolescents screened					X	
Number of adolescents enrolled					X	
Number of adolescents retained at 3-month follow-up						X

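### The post-treatment time point of the primary outcome is stated inconsistently: completion of module 8 in some places, week 8 in others, and controls have no modules

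*Protocol article*

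**What the plan says.** The protocol article places the post-treatment MASC2 in four ways.

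- **Statistical Analyses:** the mean difference in change scores runs "from baseline to the completion of module 8 (post-intervention) will be calculated with 95% CIs". One sentence covers both arms.
- **Sample Size:** the plan expects to "retain 40 adolescents (20 per arm) by module 8 completion (post-intervention"). This again covers both arms.
- **Primary Outcome Measure:** the Breathe arm is assessed at "baseline (pre-treatment), 8 weeks/end of 8^th" module. For the other arm, "Adolescents in the control group complete the MASC2 at baseline and 8 weeks after study enrolment via IRIS".
- **Table 1:** the visit is headed as 8 weeks, with follow-up at 20 weeks, and no distinction by arm.

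The section on the control condition describes a static webpage, so no control participant can complete a module 8. The co-intervention and cost questions are put at the post-intervention assessment (Secondary Outcome Measures), so they share whatever timing that assessment has.

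**The concern.** Finishing module 8 happens after randomisation and can happen only in the Breathe arm. If it triggers the assessment, adolescents who stop early give no post-treatment score and slow workers give a late one, while controls are measured by the calendar. The between-arm mean difference and its confidence interval would then not compare the groups as randomised. Controls may also take up Breathe after their 8 weeks, so a late Breathe score would have no untreated score at the same elapsed time beside it. The look-back period for co-interventions and costs could differ between arms in the same way.

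The two time points coincide only if modules are completed weekly without slippage. The plan instructs weekly use, but it also plans for half of those enrolled to drop out. Its Introduction cites a comparable adolescent programme in which, "of nine online modules available to complete within a 9-week period, the average number of completed modules was 2.9".

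**Working it through.** **1. The plan's own figures.** The Sample Size section proceeds by "assuming that 50% will refuse to participate and 50% of enrolled adolescents will drop out".

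- Enrolled: 160 × (1 − 0.5) = 80, or 40 per arm.
- Retained: 80 × (1 − 0.5) = 40, or 20 per arm.

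Both figures reproduce exactly. The arithmetic is sound; the issue is the event at which retention is counted.

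**2. The statements side by side.**

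| Place | Breathe | Control |
|---|---|---|
| Statistical Analyses | module 8 completion | module 8 completion (cannot occur) |
| Sample Size | module 8 completion | module 8 completion (cannot occur) |
| Primary Outcome Measure | 8 weeks or end of module 8 | 8 weeks after enrolment |
| Table 1 | 8 weeks | 8 weeks |

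No statement ranks one trigger above the other.

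**3. Size of the selection effect under the literal reading.** Assume that change scores in the whole Breathe arm have SD 1, that a fraction p finishes, and that the propensity to finish correlates ρ with improvement (bivariate normal). The documents give no ρ. With c = Φ⁻¹(1 − p) and λ = φ(c)/p:

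- shift in the mean = ρλ
- variance among finishers = 1 − ρ²λ(λ − c)

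For p = 0.5, c = 0, λ = 0.3989/0.5 = 0.798 and λ² = 0.637.

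| ρ | Shift (SD) | Variance | SD |
|---|---|---|---|
| 0.2 | 0.16 | 0.975 | 0.987 |
| 0.3 | 0.24 | 0.943 | 0.971 |
| 0.4 | 0.32 | 0.898 | 0.948 |

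For ρ from 0.2 to 0.4, the shift is 0.22 to 0.45 SD if 32% finish and 0.08 to 0.17 SD if 75% finish.

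With 20 per arm, the 95% CI half-width for the mean difference is t(0.975; 38) × √(2/20) = 0.64 SD. At p = 0.5 the shift is therefore a quarter to a half of the half-width.

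**4. Effect on the full-trial sample size.** The plan carries the SD forward. As an illustration, assume a standardised difference of 0.5, two-sided 5% alpha and the plan's 90% power. Then n per arm = 2 × (1.960 + 1.282)²/0.5² = 84.06, rounded up to 85. With the variance averaged over a selected and an unselected arm:

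- ρ = 0.2: 84.06 × (1 + 0.975)/2, giving 83
- ρ = 0.4: 84.06 × (1 + 0.898)/2, giving 80

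**5. How many Breathe scores at module 8?** A mean number of modules completed caps the share who can have completed all of them (Markov's inequality). The Introduction cites two trials.

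- 2.9 of 9: at most 2.9/9 = 32%; 0.322 × 40 = 12.9, about 13.
- 7.5 of 10: at most 75%; 0.75 × 40 = 30.

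The plan expects to "enroll 80 adolescents (40 assigned to each study arm") and needs 20 of those 40. Its two precedents fall on either side of that number. Applying them to Breathe is itself an assumption.

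**The case against.** The strongest reply is that module 8 completion serves merely as a label for the week-8 visit. Table 1 uses calendar points, the programme is described as 8 modules over 8 weeks, adherence is counted at 8 weeks, and the Sample Size section applies the phrase to controls, for whom it can only be a label. This has force. A reader might infer that the plan measures only Breathe finishers, but no sentence withholds the MASC2 from those who stop early, and the slash leaves a calendar reading open. What stands is that the passages differ and none settles which governs.

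Other stronger readings also lack support:

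- **That the 50% loss is not conservative.** The 2.9/9 trial points that way, but the 7.5/10 trial allows well over 20 of 40, and the plan does not define drop-out as failing to finish module 8.
- **That the bias in the mean enters the full-trial sample size.** The plan carries forward the SD, not the observed difference. An SD estimated from 20 people has a relative standard error of about 1/√(2 × 19) = 16%, larger than the 1% to 5% at issue.
- **That the completer rule contradicts the outcome.** The plan states: "We will summarize characteristics of completers (>75% of modules) and non-completers". On 8 modules this means 7 or 8, so a completer may not have reached module 8. But the rule describes engagement; it does not define who is analysed.
- **That little keeps participants on pace.** Besides the e-mail after a missed week, the plan describes automated reminders and telephone and e-mail support. These reduce slippage but do not guarantee module 8 by week 8.

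The correlation is assumed, and its sign could be negative if adolescents who improve early stop early. This is also an open-label pilot, with the between-arm difference reported descriptively. That limits the consequences, but the difference and its interval are still planned outputs.

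**Conclusion.** The point holds as an unresolved inconsistency in the timing of the primary outcome. The analysis sentence names an endpoint that half the sample cannot reach. If that wording is followed, the mean difference and its confidence interval are conditioned on a post-randomisation event in one arm. The illustrative shift of about 0.16 to 0.32 SD in the Breathe mean rests on 50% finishing and an assumed correlation of 0.2 to 0.4, and its direction is not certain. The effect on the SD used for planning is small. The number of Breathe scores available at module 8 is uncertain, with a ceiling of about 13 to 30 of 40 depending on which cited trial Breathe resembles. If week 8 is what the plan intends, the selection problem disappears once the text says so and all randomised adolescents are assessed then. Scores not collected at week 8 from those who have not finished cannot be recovered later.

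**What to change.** State one time point, 8 weeks after randomisation, for both arms. It should replace module 8 completion in Sample Size and Statistical Analyses, and the double trigger for Breathe in Primary Outcome Measure. The control sentence should count from the same origin.

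Send the MASC2 and the post-intervention co-intervention and cost questions at week 8 to every randomised adolescent, whatever the number of modules done. Analyse by allocated arm and report module 8 completion as adherence only.

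The cost is a wording change and an automated week-8 prompt. IRIS already delivers the MASC2 to controls, who have no modules. The enrolment target of 80 does not change. If all 40 per arm responded, the CI half-width would be t(0.975; 78) × √(2/40) = 0.45 SD, against 0.64 SD with 20 per arm. The drawback is that some Breathe participants would be measured before finishing all modules, so the effect may look slightly smaller.

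### The arm difference and the full-trial sample size rest on MASC2 change scores; adjusting for the baseline score already collected would be valid too and usually more efficient

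*Protocol article*

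**What the plan says.** In the protocol article, Statistical Analyses defines the comparison on the primary outcome as follows: "The mean difference in primary outcome change scores (and SDs) from baseline to the completion of module 8" (post-intervention), and this "will be calculated with 95% CIs". The next sentence sets the planning input for the later trial: "SD values from the primary outcome change scores will be used to guide the full-scale RCT sample size calculations".

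On covariates, the same section says the team "will explore potential confounders (eg, age, sex, co-morbidity) that may be adjusted for in the full-scale RCT". Baseline MASC2 is not among the examples.

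The baseline score exists in both arms. Under Primary Outcome Measure, "Adolescents in the control group complete the MASC2 at baseline and 8 weeks after study enrolment via IRIS". The treatment group completes it at baseline, at 8 weeks and 3 months after treatment. The Sample Size section justifies the 40 retained adolescents as enough to "calculate a sample size based on 90% power for a full-scale RCT".

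The article gives no SD, MCID value, baseline to week-8 correlation or full-trial sample size. It describes the 3-month retest reliability of the MASC2 as excellent, without a figure.

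**The concern.** Subtracting the baseline fixes its coefficient at 1. When the regression slope of the week-8 score on baseline is below 1, the change score over-corrects. It then keeps part of any chance baseline difference between arms, with the sign reversed, and carries extra variance. ANCOVA estimates the slope instead.

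Two outputs of the pilot are affected. One is the confidence interval for the arm difference. The other matters more: the SD passed on to the full-trial calculation, because determining that sample size is one of the six stated aims. A change-score SD describes the precision of a change-score analysis. If the later trial adjusts for baseline, as it sensibly could, that SD does not match its analysis.

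**Working it through.** **The plan's own figures.** 160 invited × (1 − 0.5) = 80 enrolled; 80 × (1 − 0.5) = 40 retained, or 20 per arm. These reproduce, and nothing below changes them.

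**Inputs.** From the article: 20 per arm analysed and 90% power for the full trial. Assumed, because not given: r from 0.5 to 0.95; two-sided alpha 0.05, in line with the 95% CIs; equal SD σ at baseline and week 8; full-trial effects of 0.5σ and 0.3σ, for illustration only.

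**Variances.** Let s0 and s1 be the baseline and week-8 SDs.
- Change score: s0² + s1² − 2·r·s0·s1
- ANCOVA residual: s1²(1 − r²)
- Difference between them: (s0 − r·s1)², which is never negative and is zero only when the slope is 1

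With s0 = s1 = σ these become 2σ²(1 − r) and σ²(1 − r²), so the ratio is (1 + r)/2 and the proportional saving in sample size is (1 − r)/2.

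**Full-trial sample size.** Per arm, n = 2·SD²·(1.960 + 1.282)²/δ², rounded up. Example at r = 0.5 and δ = 0.5σ: the change-score SD² is 1.00σ², giving 85 per arm; the ANCOVA SD² is 0.75σ², giving 64 per arm. Totals below are before dropout, change score vs ANCOVA.

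| r | variance ratio | saving | total, δ = 0.5σ | total, δ = 0.3σ |
|---|---|---|---|---|
| 0.5 | 0.75 | 25% | 170 vs 128 | 468 vs 352 |
| 0.7 | 0.85 | 15% | 102 vs 86 | 282 vs 240 |
| 0.8 | 0.90 | 10% | 68 vs 62 | 188 vs 170 |
| 0.9 | 0.95 | 5% | 34 vs 32 | 94 vs 90 |

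Rounding to whole participants makes the small totals depart slightly from the exact percentages.

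**Pilot interval at 20 per arm.** The large-sample ratio ignores the lost degree of freedom (38 to 37) and the cost of estimating a slope. Simulation of 20,000 trials for each r, with 20 per arm, gives:

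| r | simulated variance ratio | mean CI width, ANCOVA/change | narrower by |
|---|---|---|---|
| 0.5 | 0.78 | 0.879 | 12% |
| 0.7 | 0.88 | 0.935 | 6.5% |
| 0.8 | 0.92 | 0.963 | 4% |
| 0.9 | 0.97 | 0.989 | 1% |
| 0.95 | 1.00 | 1.002 | 0% |

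**Chance imbalance.** With 20 per arm the baseline mean difference has standard error √(2/20) = 0.32σ, so an imbalance of 0.3σ or more, in either direction, arises in about one trial in three. Given imbalance D, the change-score difference shifts by −(1 − r)D: at D = 0.3σ and r = 0.5 the shift is 0.15σ in size. It averages to zero over randomizations but is present in the one trial that is run.

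**Imprecision of what the pilot can supply.** An SD on 38 degrees of freedom has a 95% interval from about 18% below to 29% above its estimate, which is 0.67 to 1.66 times on the variance and hence on the sample size. From 40 completers, an estimated r of 0.7 has a 95% interval of about 0.50 to 0.83.

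**The case against.** The strongest reply is that nothing here is an error. The difference in mean change scores is unbiased under randomization and its interval is valid. The pilot attaches no test or decision rule to the arm difference, so a somewhat wider interval changes no stated decision. All of that stands.

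A reader might infer that the full trial will be made too large for its 90% power. The article does not support that. It fixes no full-trial model, SD or sample size, and says only that the change-score SDs will guide the calculation. If the later trial also analyses change scores, SD and analysis match. If it uses ANCOVA, a size based on the change-score SD is conservative. Neither case underpowers it.

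A reader might also infer that baseline MASC2 has been ruled out as a covariate. The list is introduced as examples only, so this does not follow. The article does not name it; it does not exclude it.

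The quantities could be recovered later. If baseline, week-8 and change SDs are all reported for the same completers, r = (s0² + s1² − s_change²)/(2·s0·s1). This is true, but the article commits neither to reporting them on that set nor to using them.

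Two cautions on size also stand. Excellent retest reliability may point to a high r, where the saving is only 5% to 10%; response to treatment could lower r, but the article cannot settle this. And a saving of 5% to 15% is well inside the sampling error of an SD from 40 people, so adopting a smaller residual SD at face value would give up a safety margin.

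**Conclusion.** The point holds as an efficiency improvement to a valid analysis. The article states both the estimator and the planning SD, so this is not a detail merely left to an unseen analysis plan, and the data for a better estimate are already being collected.

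The size depends on an r that the article does not give and on the equal-SD assumption. The full-trial saving also depends on that trial being analysed by ANCOVA; without that, the full-trial percentages do not apply. Over r = 0.5 to 0.9 the benefit runs from substantial to slight, and for the pilot interval it disappears near r = 0.95. The totals in the working illustrate assumed effects and are not estimates of the trial to come. The lasting gain is that the pilot would report r and the residual SD, so the full trial's sample size and analysis can be matched.

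**What to change.** 1. Add an ANCOVA of week-8 MASC2 on arm and baseline MASC2, and report the adjusted difference with its 95% CI. Keep the change-score means and SDs beside it.
2. Report the residual SD and the baseline to week-8 correlation in the same completers.
3. Base the full-trial sample size on the SD that matches that trial's planned analysis, and allow for the imprecision of an SD or correlation from about 40 completers, for example by showing the sample size across their confidence limits.
4. Name baseline MASC2 as a full-trial covariate in advance, apart from the exploratory search for other covariates.

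The cost is one extra model and one degree of freedom. No new data are needed, and the article reports enrolment as still under way, with the analysis still ahead.
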